## D.8. Sample size calculation

Sample size calculations were designed for the trial to detect a 33% absolute reduction in the annual diarrheal incidence rate in children below the age of 5 in SODIS users compared to non-users. We consider a reduction of the annual incidence of 5 to 3.33 episodes per child <5 as of significant public health importance (Bern et al. 1992). This absolute rate reduction (1.67 episodes/child/year) is even lower than what was found in the Kenyan SODIS trials (2.1 epi/ch/yr)(Conroy et al. 1999). Conroy observed 2546 diarrhoeal episodes among a total of 4382 fortnight observation periods (58.1%) in the control group (172 children). A total of 2210 episodes among 4323 observations (48.8%) were found in the intervention group (174 children) resulting in their report of a 9.3% reduction of diarrhoea in children below 6 years. By considering 26 repeated measurements of fortnight periods an approximation of the annual incidence, the Conroy findings suggest an average annual reduction of 2.1 episodes/child/year for a child in the control *versus* intervention group (14.6 *versus* 12.7 epi/ch/yr). The magnitude of diarrhea reduction we have powered the study to detect compares favorably to the achievements of other well designed interventions that influenced national diarrheal disease control programs elsewhere in developing countries (Huttly et al. 1997, Stanton and Clemens 1987).

In cluster randomized interventions, within cluster similarities may occur as a result of the spread of disease among cluster members. We have considered this aspect in the design and statistical analysis of this trial: within-cluster similarities decrease the effective sample size in comparison with that required when using individual randomization. We calculated the number of clusters based on different assumptions about cluster size (i.e. the number of subjects in each village and total person-time of observation) and varying dimensions for the coefficient of between-cluster variation of the true diarrheal disease incidence rates in each study condition. The difficulty in calculating sample size for cluster randomized trials is the process of obtaining an estimate of the between-cluster variation. The calculations presented below use baseline assumptions for within- and between-cluster variation of similar studies (Hannan et al. 1994, Simpson et al. 1995). (Table 1). We also illustrate in Table 2 how differing levels of between-cluster variation may affect sample size using procedures for sample size calculations presented in Hayes & Bennett (Hayes and Bennett 1999):

$$c = 2 + (z_{\alpha/2} + z_B)^2 \times \{ (R_0 + R_1)/y + k^2 (R_0^2 + R_1^2) \} / (R_0 - R_1)^2$$

where c = the number of clusters within each group, y = person-years of follow up in each cluster and k = coefficient of variation (sd/mean) of the true rates of diarrhea between the clusters (within each group). We assume that k is the same in both treatment arms. Without other data currently available, different (conservative) assumptions are made for the between cluster variation. More accurate estimation of the between-cluster variation (k) of the true rates of diarrhea in the clusters will be obtained from reports of diarrhea from the baseline morbidity surveys and will provide the basis for pair-matching of intervention and control villages. However, we can assume that the exposure to environmental risks of

waterborne infection is similar in the villages involved in this trial and thus, the within-village variation will be greater than the between-village variation with regard to the outcome. As a conservative approach we assume that the between-cluster variation (k) will be k=0.3 or lower.

Calculations presented below are based on an equal number of subjects being investigated in each cluster. This sample size calculation is conservative since it assumes that the data will be summarized at the cluster level prior to analysis. Analysis using mixed models making use of the within cluster information are more efficient than other approaches (Murray 1998).

**Table 1:** Number of clusters required per trial arm for different person-times of observation and different levels of between-cluster variation.  
(Based on a 33.3% reduction of the annual child-diarrheal incidence from 5 to 3.333 episodes/child/year)

| Cluster size                |                      | Coefficient for between cluster variation |          |          |
|-----------------------------|----------------------|-------------------------------------------|----------|----------|
| Person years of observation |                      | k = 0.1                                   | k = 0.25 | k = 0.34 |
| 5                           | (5 kids for 12 mth)  | 7.7                                       | 10.8     | 15.9     |
| 10                          | (10 kids for 12 mth) | 5.4                                       | 8.4      | 13.5     |
| 15                          | (15 kids for 12 mth) | 4.6                                       | 7.6      | 12.7     |
| 20                          | (20 kids for 12 mth) | 4.2                                       | 7.3      | 12.4     |
| 30                          | (30 kids for 12 mth) | 3.8                                       | 6.9      | 12.0     |

**Table 2.:** Number of clusters per treatment arm for different reductions of the annual child-diarrheal incidence rate and different level of between-cluster variation.  
(Based on 10 person-years of observation in each cluster)

| Reduction of mean annual incidence rate |                 | Coefficient for between cluster variation |          |          |
|-----------------------------------------|-----------------|-------------------------------------------|----------|----------|
| Person years of observation             |                 | k = 0.1                                   | k = 0.25 | k = 0.34 |
| 20%                                     | (1 episodes)    | 12.3                                      | 21.9     | 38       |
| 33.3%                                   | (1.67 episodes) | 5.4                                       | 8.4      | 13.5     |
| 50%                                     | (2.5 episodes)  | 3.4                                       | 4.5      | 6.5      |

**Design effect:** Ignoring clustering in this trial would turn the trial design into that of a classical clinical trial with individual randomization. The required sample size in terms of person-years of observation (y) is calculated as,

$$y = (z_{a/2} + z_B)^2 \times (R_0 + R_1) / (R_0 - R_1)^2, \text{ and}$$

would result in 23.6 year of person-time of observation in each cluster and in a design effect of ~2.4. (23.6/10)

From those calculations we conclude the following:

**Number of clusters and subjects per cluster:** We assume that the incidence rate of diarrhea in the control villages remains constant at 5 episodes/child/year and that we require 80% power ( $z_a = 0.84$ ) of detecting a significant difference ( $p < 0.05$ ;  $z_{a/2} = 1.96$ ) if the intervention reduces diarrheal incidence by 33%. We will achieve a minimum of 10 person-years of observation in each cluster, which amounts to 10 subjects per cluster observed for the duration of 12 months. Finally, considering a conservative between-cluster variation ( $k=0.2$ ) we would need 9 villages each in the intervention and control group. Based on previous experience in our Bangladesh trial (Hobbins et al. 2000a) we consider a drop out rate of one to two villages per study group and thus adjust final sample size to 22 villages (clusters); 11 in each treatment arm.

Finally, we have included 30 children in each village with the following justification:

i.) few marginal costs arise in investigating more children in each village;

- ii.) this allows us to compensate for loss of follow up of individuals;
- iii.) the study is powered to maintain its ability to detect even a 16% reduction of diarrheal incidence from 5 to 4.2 episodes at a between cluster variation of  $k=0.12$  (cf. Table 2. detailed Calculations not shown).

Thus, overall 660 households, 30 in each of the 22 villages and each with an index child under the age of 5 years enrolled in the trial will be participating in the study.

The following additional information on different parameters was considered in the sample size calculations above:

1. About 15% of the rural population in the study area are children under 5 years.(Centro Desarrollo Agropec., 1994).
2. The incidence of diarrhea in children <5 years of age is estimated from different national studies at 4-5 (episodes/child/year (S.N.S.I.)(Prado and O'Ryan 1994, Quick et al. 1999).

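### D.8 calls the sample size conservative because data are summarised by village, but with equal village sizes an unadjusted child-level model is no more precise; the real reserve lies elsewhere and depends on k

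*Protocol*

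**What the plan says.** Section D.8 of the protocol introduces its sample size tables with three linked statements. On cluster size: "Calculations presented below are based on an equal number of subjects being investigated in each cluster". On the standing of the result: "This sample size calculation is conservative since it assumes that the data will be summarized at the cluster level prior to analysis". In support of that: "Analysis using mixed models making use of the within cluster information are more efficient than other approaches". No size is given for the efficiency gain.

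The number of villages is then derived with two-sided 5% significance and 80% power for a fall from 5 to 3.33 episodes per child per year. On follow-up, D.8 says "We will achieve a minimum of 10 person-years of observation in each cluster". The final step begins "Finally, considering a conservative between-cluster variation", sets k=0.2 and arrives at 9 villages per arm. This is raised to 11 because one to two villages per arm may drop out. Thirty children per village are enrolled. Earlier in D.8, the text following the formula gives the conservative assumption as k=0.3 or lower.

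Section D.9 names village-level incidence rates as the unit of analysis for comparing rates. It also plans a child-level Poisson GEE with a compound-symmetry working correlation and robust variance. Section A mentions mixed effects models.

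**The concern.** SODIS is allocated to whole villages, so every child in a village has the same treatment and the comparison is between villages. If every village contributes the same number of children, modelling the children individually recovers nothing that the village mean has not already used. The reason that D.8 gives for calling its calculation conservative then fails.

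What is at stake is how the power statement is read. A funder or ethics board told that the calculation is conservative will take true power to be somewhat above 80%, whatever k turns out to be. Whether it is depends on the number of villages, the number of children and k. D.8 calls two different values of k conservative, and they give materially different answers.

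**Working it through.** **Inputs (all from D.8).** R0 = 5 and R1 = 3.333 episodes per child-year; z values 1.96 and 0.84; y = 10 person-years per village in the calculation and 30 as enrolled; k = 0.2 (used for sizing) and k = 0.3 (stated bound); 9 villages per arm computed, 11 planned, loss of one to two per arm allowed for.

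**1. Reproduce the protocol's figure.** The formula is c = 2 + (1.96 + 0.84)² × {(R0+R1)/y + k²(R0²+R1²)} / (R0−R1)².

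- (R0+R1) = 8.333; (R0²+R1²) = 25 + 11.11 = 36.11; (R0−R1)² = 2.778; 2.8² = 7.84.
- At k=0.2, y=10: 0.8333 + 0.04 × 36.11 = 2.278, so c = 2 + 7.84 × 2.278/2.778 = 8.43, that is, 9 villages per arm. The stated number is reproduced.

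A reader checking this against Tables 1 and 2 will find 8.4 in the column headed k=0.25. The columns headed 0.25 and 0.34 match the formula at 0.2 and 0.3; at the labelled values, with y=10 and a 33.3% reduction, it gives 10.7 and 16.1. That labelling is a separate matter, and the body text's k=0.2 is consistent with the formula.

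**2. Does a child-level model gain anything?** With m children in every village and c villages per arm, the variance of an arm mean is

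(between-village variance + within-village variance / m) / c.

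This holds for the mean of village means. It also holds for an unadjusted mixed model or exchangeable GEE, because equal sizes give every village equal weight. The within-village part is already in the protocol's formula as (R0+R1)/y. Relative efficiency is 1.00 and no villages are saved.

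Simulated balanced trials (11 villages per arm, 10 or 30 children, k = 0.2 or 0.3) agree:

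- In 150 fitted trials per setting, the mixed-model difference equalled the difference in village means to about 1e-14, and the GEE log rate ratio equalled the log ratio of arm means to about 1e-15.
- In 2,000 trials per setting, the closed-form mixed-model standard error equalled the village-mean one to 3e-16. The only exceptions were 18 trials (10 children, k=0.2) where the between-village variance estimate was zero or negative.
- Standard errors reported by fitted mixed models differed from the village-mean ones by up to 27% in single trials. That concerns how a fit estimates the variance; the estimates themselves, and so their spread across trials, were the same.

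**3. Where the reserve is.** Rearranging the formula, power = Φ( √[ (c−2) × 2.778 / {8.333/y + 36.11 k²} ] − 1.96 ).

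With y=30 the term in braces is 0.278 + 1.444 = 1.722 at k=0.2, and 0.278 + 3.25 = 3.528 at k=0.3. For example, at k=0.3 and c=11: 9 × 2.778/3.528 = 7.09, square root 2.66, less 1.96 = 0.70, giving 76%.

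| Villages per arm (30 child-years each) | k=0.2 | k=0.3 |
|---|---|---|
| 11 | 97% | 76% |
| 10 | 95% | 71% |
| 9 | 92% | 65% |

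With 10 person-years per village and 11 villages per arm, the figures are 91% at k=0.2 and 70% at k=0.3.

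**4. Villages needed at k=0.3.** With y=30: 2 + 7.84 × 3.528/2.778 = 11.96, so 12 against 11 planned. With y=10 it is 13.5.

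**5. Largest k that keeps 80% power with 11 per arm and y=30.** Set 9 × 2.778 / {0.278 + 36.11 k²} = 7.84. Then 36.11 k² = 3.189 − 0.278 = 2.911 and k = 0.284, about 0.28.

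**The case against.** The best defence is that the disputed sentence does no work. D.8 puts no size on the efficiency gain and takes no credit for it; the village count comes from the formula alone. Deleting the sentence would change no number in the design. That stands. A reader might infer that the sample size leans on a reserve that does not exist, or that 9 villages is wrong. The documents support neither.

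Nor is the plan without a reserve. At its own sizing value, k=0.2, enrolling 30 children takes power well above 80% even after two villages per arm are lost. D.8 gives 0.3 as a ceiling, not an expected value. This stands too, and it is why the k=0.3 figures should not be quoted alone.

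It can also be said that the actual analysis will not be the balanced, unadjusted case. D.8 expects some loss of children, and D.9 plans an offset for time at risk and adjustment for child and village covariates. Part of this stands. Weighting for unequal sizes gains little: for assumed coefficients of variation in village size of 0.1 to 0.5, unweighted means lose at most 1.2% efficiency at 30 children and 4.7% at 10. Covariate adjustment could gain more, but it can also be done in a two-stage village-level analysis, and D.8 does not offer it as the reason. Pair-matching on baseline diarrhoea (D.1, D.6.b, D.10) may reduce the relevant between-village variation by an unknown amount.

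**Conclusion.** The point holds as a misstatement of why the calculation is conservative. Under D.8's own equal-size assumption, the gain from an unadjusted child-level model over village summaries is zero. The margin over 80% power comes from 30 rather than 10 children per village, plus two villages per arm that are already earmarked for dropout. It is ample at k=0.2 (92% to 97%) and insufficient at k=0.3 (65% to 76%), with the crossover at about k=0.28 if all 11 villages per arm remain.

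A reader might go further and attribute the shortfall at k=0.3 to the mistaken efficiency claim, or conclude that the trial is underpowered. Neither follows. The shortfall comes entirely from k and would be the same had the sentence never been written; and k is unknown until the baseline surveys.

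The power figures rest on the protocol's formula, with k as between-village variation within an arm before matching and Poisson variation within villages. They leave out any gain from matching or covariates. They also leave out any inflation from repeat episodes in the same child, which would work the other way: an assumed inflation of 2 to 4 times raises the requirement at k=0.2 with 30 child-years from 6.9 to between 7.6 and 9.2 villages per arm, still within 11.

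**What to change.** In D.8, delete the sentence calling the calculation conservative and the one on mixed-model efficiency. Alternatively, keep the word conservative but rest it on the enrolment of 30 children per village when the calculation used 10 person-years.

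Reconcile the two values of k that D.8 calls conservative, and say which one the design is meant to withstand. State power with 30 child-years per village at both: 97%, 95% and 92% at k=0.2, and 76%, 71% and 65% at k=0.3, for 11, 10 and 9 villages per arm. Add that with 11 per arm power stays at or above 80% only up to k of about 0.28, and that these figures take no account of pair-matching or covariate adjustment.

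The cost is a few sentences and a less favourable stated figure at k=0.3. This edit changes no village count, enrolment target or analysis.

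### Section D.8 is inconsistent on the between-village variation k: table columns are headed with the wrong k, and 11 villages per arm give less than 80% power at the protocol's own bound of k=0.3

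*Protocol*

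**What the plan says.** All of this stands in Protocol section D.8.

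- **Formula.** The number of villages per arm comes from the printed Hayes and Bennett expression for rates, with an additive term of 2. The design values are two-sided 5% significance, 80% power, and a fall from 5 to 3.333 episodes per child per year. It assumes that "the incidence rate of diarrhea in the control villages remains constant at 5 episodes/child/year".
- **k before the tables.** "As a conservative approach we assume that the between-cluster variation (k) will be k=0.3 or lower".
- **Tables 1 and 2.** Table 1 gives the "Number of clusters required per trial arm for different person-times of observation and different levels of between-cluster variation". Both tables head their columns k = 0.1, 0.25 and 0.34.
- **k after the tables.** The final number rests on k=0.2, again called conservative, with at least 10 person-years per village: "we would need 9 villages each in the intervention and control group".
- **Village losses.** "we consider a drop out rate of one to two villages per study group", so the total becomes 22 villages, 11 per arm. Thirty children per village are enrolled.
- **Design effect.** Ignoring clustering "would result in 23.6 year of person-time of observation in each cluster and in a design effect of ~2.4", obtained as 23.6/10.

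**The concern.** Neither value of k used in the text (0.2 and 0.3) appears as a column heading, so a reader cannot follow the step from the tables to 9 villages. A reader who takes the headings at face value is given too few villages for k=0.25 and k=0.34. The word conservative is attached both to an upper bound of 0.3 and to a value of 0.2 well inside it, and the sample size rests on the smaller one.

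What is at stake is how a null result would be read. Section D.10 describes the sample as ample, and the introduction expects the findings to bear on international support for solar disinfection. If the true k is near the protocol's own bound, the chance of missing a one-third reduction is larger than D.8 suggests.

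**Working it through.** **Inputs (all from D.8).** z = 1.96 and 0.84, so (1.96 + 0.84)² = 7.84. R0 = 5 and R1 = 3.333, so R0 + R1 = 8.333, R0² + R1² = 36.11 and (R0 − R1)² = 2.778. y is person-years per village.

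**Formula.** c = 2 + 7.84 × V / 2.778, with V = 8.333/y + 36.11 k².

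**1. The protocol's own figure.** For k=0.2 and y=10, V = 0.833 + 1.444 = 2.278 and c = 2 + 6.43 = 8.43, rounded up to 9. It reproduces.

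**2. The table headings.** Villages per arm for a 33.3% reduction:

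| y | printed under 0.25 | formula, k=0.20 | formula, k=0.25 | printed under 0.34 | formula, k=0.30 | formula, k=0.34 |
|---|---|---|---|---|---|---|
| 5 | 10.8 | 10.8 | 13.1 | 15.9 | 15.9 | 18.5 |
| 10 | 8.4 | 8.4 | 10.7 | 13.5 | 13.5 | 16.1 |
| 15 | 7.6 | 7.6 | 9.9 | 12.7 | 12.7 | 15.4 |
| 20 | 7.3 | 7.3 | 9.5 | 12.4 | 12.4 | 15.0 |
| 30 | 6.9 | 6.9 | 9.2 | 12.0 | 12.0 | 14.6 |

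Table 2 shows the same pattern. Its 20% row prints 21.9 and 38, which are the k=0.20 and k=0.30 results; k=0.25 and 0.34 would give 29.2 and 46.2. Solving every cell of these two columns for k gives 0.199 to 0.201 and 0.299 to 0.301. An additive term of 1 does not rescue the headings, because the implied k then changes from row to row of Table 2. The k=0.1 column is correctly headed.

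**3. Requirement at the bound, k=0.3.**
- y=10: V = 0.833 + 3.25 = 4.083, so c = 2 + 11.52 = 13.5.
- y=30: V = 0.278 + 3.25 = 3.528, so c = 2 + 9.96 = 12.0.

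Both exceed 11 before any village is lost.

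**4. Power from the same formula.** Power = Φ(√[(c − 2) × 2.778 / V] − 1.96). For example, with c=11, y=30 and k=0.3: √(9 × 2.778/3.528) = 2.66, and Φ(0.70) = 76%.

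| k | 11 per arm, y=10 | 11 per arm, y=30 | 9 per arm, y=10 | 9 per arm, y=30 |
|---|---|---|---|---|
| 0.20 | 91% | 97% | 83% | 92% |
| 0.25 | 81% | 88% | 71% | 79% |
| 0.30 | 70% | 76% | 59% | 65% |

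The largest k that still gives 80% power is 0.255 (y=10) or 0.284 (y=30) with 11 per arm, and 0.214 or 0.247 with 9.

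**5. The design effect.** The formula for individual randomisation gives 7.84 × 8.333/2.778 = 23.5 person-years (printed as 23.6). That is the total for one arm. D.8 describes it as belonging to each cluster and divides it by 10 person-years per village. A per-arm total over a per-village amount is not the ratio of clustered to unclustered sample size.

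**The case against.** **The sizing is right for the k it uses.** This stands. Nine villages is correct for k=0.2, and with 30 person-years the power at that k is 97% with 11 villages per arm and 92% with 9. The wrong headings did not carry into the number chosen.

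**The headings may not be the sponsor's error.** They look like 0.2 and 0.3 with one digit added and could be an artefact of converting the file to text. That cannot be settled here. If so, the rest is untouched: the two conservative values are in the prose, and the cells 13.5 and 12.0 still exceed 11.

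**The shortfall at k=0.3 is small before losses.** With 30 person-years it is 12 villages against 11. An additive term of 1 in place of the printed 2 gives 80.1%, and an unpaired noncentral-t calculation gives 79.9%. This is fair, but D.8 foresees losing one to two villages per arm. With 10 left these variants give about 76%, and with 9 about 71%.

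**Two stronger readings are tempting.** A reader might infer that the protocol promises 80% power at k=0.3. It does not: it attaches 80% to k=0.2 and names 0.3 only as a bound. A reader might also infer that each lost village destroys a matched pair, so that the loss allowance fails. The rate comparisons and regressions described in D.9 do not analyse pairs, so they keep every surviving village. At k=0.2 and 30 person-years even 7 villages per arm would give 81%.

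**Re-estimating k is already planned.** D.8 says that the baseline survey will give a better value. That stands, and the fix builds on it.

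**Conclusion.** The point holds as an inconsistency in D.8, not as an arithmetic error in the 9 villages. Two columns in each table carry headings that the printed formula contradicts; at 30 person-years the true requirements for k=0.25 and 0.34 are 9.2 and 14.6 villages per arm, not 6.9 and 12.0. Two different values of k are both called conservative. At the larger one, 11 villages per arm give 70% (10 person-years) or 76% (30 person-years), falling to 59% or 65% if 9 remain. The design effect is misdefined, although it does not enter the derivation of 9 or 11.

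These figures rest on the printed formula with its additive 2, the stated rates, the same k in both arms, equal person-years per village and no credit for matching. Effective matching could lower the relevant k, but D.8 takes no such credit.

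**What to change.** 1. Head the second and third columns of Tables 1 and 2 k=0.20 and k=0.30.
2. Use one planning k throughout D.8, and stop calling 0.2 conservative beside a bound of 0.3.
3. State power at 30 person-years per village for 11 and 9 villages per arm: 97% and 92% at k=0.2, 88% and 79% at k=0.25, 76% and 65% at k=0.3.
4. Delete the design effect, or recompute it with both quantities on the same basis and say how the additive 2 is treated.
5. When k is re-estimated from the eight-week baseline survey, as already planned, record the resulting detectable effect.

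The cost is protocol wording and relabelled headings in two tables. No extra villages are needed. The downside is a less favourable stated power.

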Ability to detect a reduction in disease incidence: We have clarified our presentation of impact measures. Because of our choice of outcome measure, specifically the absolute reduction in the annual incidence of child diarrhea (episodes/child/year), our study is powered to detect a smaller reduction (1.67 episodes/child/year) than that detected in the Kenyan trials (2.1 epi/ch/yr). These calculations are detailed in the body of the grant (Section D.8.). An important difference in the presentation of the impact measures is that the Conroy study in Kenya focused on the two-week period prevalence of diarrhea whereas the outcome for our study will be annual incidence rates of diarrheal. Conroy observed a 9.3% rate reduction in their Kenyan under-5-population comparing incidence rates in control and intervention groups (58.1% vs 48.8%) (Conroy et al. 1999). By transforming the Conroy data on two-week period prevalences into a reduction of the annual incidence for child diarrhea (episodes/child/year) their findings suggest an average reduction of 2.1 episodes/child/year for a child in the intervention *versus* the control group (12.1 *versus* 14.8 epi/ch/yr). This reduction in absolute number of annual episodes of diarrhea compares favorably to the 1.67 episodes/child/year that our trial is designed to detect. The difference in relative magnitude of reduction between the studies in Kenya and our proposal, thus, derives from the different baseline rates of childhood diarrhea in the two settings.

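### Section D.8 claims a detectable reduction of 16% at k = 0.12, but the plan's own formula needs 13.3 villages per arm against 11 planned, so power is about 71%

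*Protocol*

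**What the plan says.** Section D.8 sizes the trial for a fall from 5 to 3.33 episodes per child-year. It gives a sample size formula, "where c = the number of clusters within each group, y = person-years of follow up in each cluster and k = coefficient of variation", and applies it in Tables 1 and 2. The planning values are a control rate held at 5, two-sided 5% significance and 80% power. Nine villages per arm are raised to 11 to allow for losing one or two in each arm.

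The section then gives three reasons for following 30 children per village. The third is that "the study is powered to maintain its ability to detect even a 16% reduction of diarrheal incidence from 5 to 4.2 episodes" at k = 0.12. Its only support is a pointer: "Table 2. detailed Calculations not shown".

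The 33% target is introduced thus: "Sample size calculations were designed for the trial to detect a 33% absolute reduction in the annual diarrheal incidence rate". It is set beside earlier trials in Kenya: "This absolute rate reduction (1.67 episodes/child/year) is even lower than what was found in the Kenyan SODIS trials", given there as 2.1. The introduction to the revised application says the same: "our study is powered to detect a smaller reduction (1.67 episodes/child/year) than that detected in the Kenyan trials".

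**The concern.** The third reason is a numerical power claim with no calculation behind it, and the table it points to suggests the opposite. On 10 person-years per village, Table 2 already asks for 12.3 villages per arm for a larger reduction (20%) at a smaller k (0.1). If the claim is wrong, readers will credit the trial with a sensitivity it does not have. That matters most if the result is null, because the introduction expects the findings to influence whether international support for solar disinfection continues.

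The Kenyan comparison adds to the same impression. It sets absolute reductions side by side although the baseline rates are far apart, while section D.5 evaluates the primary outcome as a ratio of incidence rates.

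**Working it through.** **Inputs, all from section D.8.** z values 1.96 and 0.84, so (1.96 + 0.84)² = 7.84; R0 = 5; R1 = 4.2; k = 0.12; y = 30 person-years per village (30 children for 12 months); 11 villages per arm.

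**Formula.** c = 2 + 7.84 × V, where V = {(R0 + R1)/y + k²(R0² + R1²)}/(R0 − R1)².

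**Check against the plan's tables.** For 5 to 4 with y = 10 and k = 0.1: c = 2 + 7.84 × (0.9 + 0.41)/1 = 12.27; Table 2 prints 12.3. For 5 to 3.333 with y = 30 and k = 0.1: c = 3.80; Table 1 prints 3.8. The k = 0.1 columns reproduce to within 0.1 village, so the formula is being read as intended. The columns headed 0.25 and 0.34 reproduce only with k = 0.2 and k = 0.3. That labelling problem does not affect this point.

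**The 16% claim.**
- V = (9.2/30 + 0.0144 × 42.64)/0.64 = (0.3067 + 0.6140)/0.64 = 1.4386.
- c = 2 + 7.84 × 1.4386 = 13.3, so 14 villages per arm against 11.
- Power with C villages per arm is Φ(√((C − 2)/V) − 1.96).
  - C = 11: Φ(2.501 − 1.96) = 70.6%
  - C = 10: Φ(2.358 − 1.96) = 65.5%
  - C = 9: Φ(2.206 − 1.96) = 59.7%
- At k = 0.10, c = 10.98. This is the largest k at which 11 villages give 80%.
- With 11 villages, power for the same 16% is 39% at k = 0.2 and 22% at k = 0.3.

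**Reduction detectable at 80% power, y = 30** (solving c = C for R1):

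| Villages per arm | k = 0.12 | k = 0.2 | k = 0.3 |
|---|---|---|---|
| 11 | 17.8% | 25.4% | 34.8% |
| 9 | 20.0% | 28.4% | 38.8% |

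**Main design.** For 5 to 3.333 at k = 0.2 and y = 30, V = 0.62. Power is Φ(√(9/0.62) − 1.96) = 97% with 11 villages and Φ(√(7/0.62) − 1.96) = 92% with 9.

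**Scale of the 33%.** 1.67/5 = 33% is a relative reduction. The absolute reduction is 1.67 episodes per child-year.

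**Kenyan figures.**
- Section D.8 prints 48.8% for 2210 of 4323; the quotient is 51.1%.
- The introduction gives 14.8 against 12.1, a difference of 2.7. Section D.8 gives 14.6 against 12.7, a difference of 1.9. Both are described as 2.1.
- Dividing the section D.8 counts by the numbers of children gives 2546/172 = 14.8 and 2210/174 = 12.7, which do differ by 2.1.

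**The case against.** The shortfall is moderate: 16% becomes about 18%. Without the added constant of 2, the formula gives 11.28 villages and 79% power. Villages are also paired on baseline diarrhea, while k in the formula is the variation within an arm. If pairing removed about 30% of the between-village variance (an assumption), the effective k would be 0.10 and the claim would hold. Section D.8 itself calls its method conservative. None of this rescues the statement as written, because the plan's formula includes the constant and the plan puts no figure on any gain from matching. A one-sided 5% test would need only 10.9 villages, but the plan uses 1.96.

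The Table 2 pointer should not be pressed further. On Table 2's 10 person-years the claim would need 20.8 villages, but the statement is a reason for enrolling 30 children, so 30 person-years is the fair basis.

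A reader might also call the Kenyan comparison false. The documents do not support that. It is expressly about absolute reductions, 1.67 is below 2.1, and it is also below 1.9 and 2.7. The introduction attributes the difference in relative effect to the different baseline rates, and section D.6.d makes the rate difference a stated effect measure. The comparison is true but gives weak reassurance about a rate ratio.

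**Conclusion.** The 16% claim is wrong by the plan's own formula. It needs 13.3 villages per arm where 11 are planned, and power is about 71%, falling to about 66% or 60% with one or two villages lost per arm. This rests on the plan's stated constants, 30 person-years in every village, and no credit for matching. The sample size itself does not depend on the claim, and the 33% design at k = 0.2 keeps ample power.

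The '33% absolute' wording and the Kenyan inconsistencies are real but secondary. That 1.67 is below 2.1 holds only on the absolute scale, against a much higher baseline. It does not show that the trial could detect the Kenyan relative effect at a baseline of 5.

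Three stronger inferences should be resisted:
- **The 16% claim promises to detect a Kenya-sized effect.** The statement does not mention Kenya.
- **The trial needs at least twice the Kenyan relative effect.** The introduction describes the Kenyan outcome as two-week period prevalence, and a ratio of prevalences is not a ratio of incidence rates. If onsets were Poisson (an assumption), 58.1% against 48.8% would mean a rate about 23% lower, and 58.1% against 51.1% about 18% lower. The detectable reductions above, 18% at k = 0.12 and 25% at k = 0.2, are not twice such figures.
- **A null result could not exclude the Kenyan effect.** That would depend on its confidence interval.

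**What to change.** Delete the third reason in section D.8, or restate it: at 80% power, two-sided 5% and 30 person-years per village, the detectable reduction is about 18%, 25% and 35% at k = 0.12, 0.2 and 0.3 with 11 villages per arm, and about 20%, 28% and 39% with 9. Show the calculation.

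In the same edit:
- Describe the 33% reduction as relative and give 1.67 episodes per child-year as the absolute figure.
- Check the Kenyan counts, percentages and annual rates against the cited source, and make section D.8 and the introduction agree. The protocol alone cannot show whether the count or the percentage is wrong.
- Add to the Kenyan comparison, in both places, that it is on the absolute scale at a higher baseline and does not establish power for the Kenyan relative effect at a baseline of 5.

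The cost is protocol wording and a less favorable stated sensitivity. Enrollment, allocation, endpoint and analysis do not change.
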